### 2.12. Data Management

The data obtained from the participants will be included in an SPSS database (version 25) (IBM, Chicago, IL, USA). Data will be entered by the lead researcher, who will be the only person with access to the database.

Patients will be coded according to the order in which they join the study, following number allocation, through randomization.

Prior to statistical analysis, in order to improve the quality of data collected, the database will be debugged with the summarize function, identifying outliers, and the analysis of losses.

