### 2.7. Blinding

Both clinicians/caregivers and research nurses will be informed of the group to which each participant is assigned due to their involvement in facilitating the care intervention for each group. However, non-caregiver researchers and those responsible for processing and analyzing the data will be blinded to assignment.

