### 2.15. Monitoring

An interim analysis is performed on the primary endpoint when 20% of patients have been randomized. The idea is to be able to identify an increase in HIV incidence in the control group, such as other potential hazard events in all participants. In that case, the study would come to a halt. The main investigator will have unblinded access to data and will discuss the results of the interim analysis with the research team.

The trial will not be stopped in case of futility related to the outcome variables because kangaroo care is the current intervention in the neonatal units due to clinically proven benefits, so futility is not sustainable.

The main investigator has the ultimate authority to stop or modify the trial and to ensure the protocol’s continued. He will follow up with all participants, and he will check all kangaroo care sessions are completed as it is referred to in the protocol. If that is not the case, the session will be discarded.

Changes on the protocol will be notified to all team members immediately and keeping all documentation standardized. All updated versions will be available in a digital form, and team members will be noticed during practical and theoretical lectures.

Safety and complications were monitored by identifying kangaroo potential adverse events noted down in the Data Collection Logbook (DCL), such as hypothermia, continuous hemodynamic instability during kangaroo care, or accidental displacement of any therapeutic device. Those events will be collected and analyzed in the first 24 h by the investigator in charge of the session, notifying the main investigator. The main investigator will record this adverse event on the study database, taking the actions required according to the severity and impact.

A committee in charge of data monitoring has not been created, the tracking is carried out by the research team. Non-audits have been scheduled.

Preliminary analyses every 20 new participants will be done to discard a rising HIV incidence in the control group, which would mean the study would come to a standstill.

Established withdrawal criteria are hypothermia or a Kangaroo care session less than 60 min.

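### Sections 2.7, 2.12 and 2.15 conflict on blinding: as written, data entry, cleaning and session exclusion are not blinded, and blinded analysis would need a masked extract that the plan does not provide for.

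*Protocol article*

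**What the plan says.** Section 2.7 (Blinding) accepts that clinicians, caregivers and research nurses know the group, then states that "non-caregiver researchers and those responsible for processing and analyzing the data will be blinded to assignment".

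Section 2.12 (Data Management) states: "Data will be entered by the lead researcher, who will be the only person with access to the database". It also plans a cleaning step before analysis, covering outliers and losses, and codes patients by the order in which they join. Section 2.6 keys the randomisation list to participant IDs 1 to 70.

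Section 2.11 (Data Collection Methods) lists position, prone or lateral, among the variables collected at every session.

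Section 2.15 (Monitoring) says of the interim analysis: "The main investigator will have unblinded access to data and will discuss the results of the interim analysis with the research team". For adverse events it says: "The main investigator will record this adverse event on the study database". On session conduct, "he will check all kangaroo care sessions are completed as it is referred to in the protocol", and then: "If that is not the case, the session will be discarded". The same section reports no data monitoring committee and no scheduled audit.

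**The concern.** Position cannot be hidden from those at the bedside, so keeping data handling and analysis blind is one of the few protections this trial can still claim against knowledge of the arm. Section 2.7 claims it. Sections 2.12 and 2.15 put entry, database access, unblinded data and the session check in what appears to be one pair of hands.

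What is at stake is discretion. Someone must decide whether a reading is an outlier, whether a session was conducted as the protocol requires, and which infants enter the intention-to-treat and per-protocol sets. In a non-inferiority trial with a margin of 0.2 °C and an assumed SD of 0.16 (section 2.5), decisions that lean even slightly one way on temperature can move the result towards non-inferiority. If the person deciding knows both arm and temperature, readers cannot exclude that, however careful the decisions were.

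**Working it through.** The plan states no figure on this point. The check is whether the statements can all be true together.

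1. **Who can handle the data?** Under 2.12, only the lead researcher enters data and opens the database. Read literally, the cleaning described there falls to that person too.
2. **Does that person know the arm?** Yes, by two routes. Position is recorded for each session (2.11). Patient codes follow order of entry (2.12), which is the ID that indexes the randomisation list (2.6). No masked arm code is described.
3. **Is the lead researcher the main investigator?** The article does not say so. But 2.15 has the main investigator recording on the study database, which 2.12 opens only to the lead researcher. Either they are one person, or 2.12 and 2.15 conflict on access as well. Step 2 holds in both cases.
4. **Who checks sessions?** The main investigator (2.15), with discarding as the consequence. The same section says "The main investigator will have unblinded access to data".
5. **What does 2.7 require?** That "those responsible for processing and analyzing the data will be blinded to assignment". Processing (entry, cleaning, exclusion) fails this by steps 1, 2 and 4. Analysis can meet it only if someone else receives a masked file, which sole access does not provide for.

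**Worst-case illustration of sensitivity.** Inputs from 2.5: SD 0.16, margin 0.2 °C, 35 per arm. Assumptions: normal data; true lateral deficit equal to the margin; a pooled t-test of H0: mean(lateral) − mean(prone) = −0.2, with t = (difference + 0.2) / SE; and the coldest records removed from the lateral arm only.

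One record per infant (100,000 simulated trials):

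| Coldest lateral infants removed | Shift in mean, °C | False non-inferiority, one-sided 0.05 | One-sided 0.025 |
|---|---|---|---|
| 0 | 0 | 5.1% | 2.5% |
| 1 | 0.010 | 8.9% | 4.9% |
| 2 | about 0.018 | 13.3% | 7.8% |
| 3 | 0.026 | 18.5% | 11.5% |

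Section 2.15 discards sessions, however, and 2.8 allows repeated sessions over five days. Assume 3 or 5 sessions per infant, a within-infant correlation of 0.3 or 0.5, and analysis of infant means. Removing the two coldest lateral sessions then shifts the mean by about 0.003 to 0.005 °C. False non-inferiority becomes about 6–8% instead of 5%, or 3–4% instead of 2.5%. The session counts and correlations are assumptions; the article gives neither.

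**The case against.** **A masked extract is not forbidden.** Sole access to a master file is an ordinary confidentiality clause, and 2.7 names separate people who process and analyse. An article may leave the mechanics of an extract to the full protocol. This stands for the analysis step: a reader might infer that blinded analysis is impossible under this plan, and the text does not support that. It does not rescue entry, cleaning and session exclusion, which 2.7 also covers by referring to processing.

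**One person or two.** That the lead researcher and main investigator are the same is an inference. This stands, but whoever enters the data still sees position.

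**Discarding follows a rule.** Section 2.15 describes a compliance check, not a free choice, and the explicit removal criteria are hypothermia and a session under 60 minutes. The unblinded access is mentioned in the interim-analysis paragraph and may be confined to it. This partly stands: the duration criterion is objective, but the check is on conduct according to the protocol as a whole, which leaves room for judgement. Removal for hypothermia is selection on the outcome whoever is blinded, so it is a separate matter and adds no weight here.

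**The simulated error rates exaggerate.** A reader might take 13% or 18.5% as the trial's real error rate. The document does not support that. Those rows remove whole infants, always the coldest, from one arm only, and nothing suggests such behaviour. The session-level figures are closer to the stated mechanism and much smaller, and they too are a worst case.

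**Other protections exist.** Temperature is read by instrument (2.11), and both intention-to-treat and per-protocol analyses are planned (2.13). Both are true, but neither blinds decisions on which records count.

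**Conclusion.** The concern holds in a limited form. Sections 2.7, 2.12 and 2.15 cannot all be followed as written. Blinded processing is claimed but not delivered for entry, cleaning and session exclusion. Blinded analysis remains possible, but only through a masked extract that the sole-access statement does not provide for.

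This rests on printed statements that conflict, not on detail missing from the article. Treating the lead researcher and main investigator as one person is likely but is not needed for the part on data entry. No actual bias can be estimated, and no misconduct is implied. The point is that a stated safeguard is not in place and can be restored cheaply. It should be corrected; it does not by itself invalidate the design.

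**What to change.** Reconcile the three sections along these lines:

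- State that the lead researcher holds the unblinded database, and whether this is the main investigator of 2.15.
- The lead researcher releases a locked extract to the blinded analysts of 2.7, with arm coded A/B, position removed and IDs re-keyed so that they no longer link to the randomisation list.
- Because adherence cannot be judged without some information on position, put an arm-neutral yes/no flag in its place: held in the allocated position or not.
- Make and log outlier, session-validity and analysis-set decisions on that extract before the code is opened.
- Do not share interim results by arm with those analysts. Section 2.15 now has them discussed with the research team.

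If this cannot be done, restrict the claim in 2.7 to the steps that really are blinded, or delete it.

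The cost is a few sentences, one coded export and a decision log, using people the plan already names. Sample size, treatment and data collection do not change.

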### 2.13. Statistical Analysis

Normality associated with each quantitative variable will be analyzed using the test Kolmogorov–Smirnov test.

A descriptive analysis will be performed of the demographic and clinical characteristics of subjects in both treatment groups: quantitative variables will be described by mean or median and their dispersion measurements, standard deviation or interquartile range, respective, as appropriate. Qualitative variables will be described by absolute frequencies and percentages. The descriptive analysis will be accompanied by the 95% confidence interval.

Prior to testing hypotheses, we will check whether both groups are homogeneous in terms of the baseline characteristics, using Student’s *t*-test or Mann–Whitney U for quantitative variables or ANOVA or Kruskal–Wallis if the variable does not follow normal distribution, and if statistically significant differences are found, we will continue with post hoc Bonferroni contrasts or weighted comparisons with Mann–Whitney U. Chi-squared will be used for qualitative variables.

If the groups are heterogeneous, confounding factors will be defined to adapt the final analysis to the main variable.

The effectiveness of KC modified lateral position compared to the KC conventional prone position will be assessed, calculating axillary temperature variation (Student’s t-test or Mann–Whitney U), level of pain (Student’s *t*-test or Mann–Whitney U), and IVH development (Chi-squared) in both groups.

Intention to treat (NNT) and protocol analyses will be performed. Should the results be conflicting, protocol deviations and/or breaches will be analyzed.

Safety analysis in relation to adverse events will be calculated using Pearson’s Chi-squared test or Fisher’s exact test as appropriate.

An explanatory model with stepwise linear regression will be created based on a significance level of 0.1, and confounding variables and their level of importance will be determined.

The statistical significance level will be *p* < 0.05. Data will be analyzed with the Statistical Package for the Social Sciences-IBM SPSS^®^ program version 25.0 (IBM, Chicago, IL, USA).

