## 2. Material and Methods

### 2.1. Aim

The main aim of this study is to assess the efficacy of the modified kangaroo care lateral position on the thermal stability of preterm infants versus conventional kangaroo care prone position. Secondary proposed aims are (a) to compare the number of intraventricular hemorrhage events in relation to the assigned group, prone or lateral position; and (b) to assess the effectiveness of kangaroo care lateral position in alleviating pain versus conventional prone kangaroo care.

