### 2.2. Design

The study is designed as a non-inferiority randomized parallel clinical trial.

The CONSORT guidelines for randomized controlled trials will be used. This protocol also adheres to the SPIRIT guidelines (Supplementary Materials: checklist SPIRIT).

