### 2.5. Sample Size

The primary outcome was the neonatal body temperature difference between KC prone position and KC lateral position. The sample size was calculated to achieve an 80% statistical power with an α of 0.05 to detect a 0.3 °C difference in the body temperature (DS 0.16) [5,13], and the non-inferiority margin was set at a 0.2 difference in body temperature [13]. In addition, we estimated a 10% loss to follow-up, so the sample size calculated is 35 participants in each group.

Additionally, the sample size was calculated to the secondary outcome; it was the difference in neonatal pain level between KC prone position and KC lateral position. With the same power an α to detect 0.83 points (DS 1), the non-inferiority margin was set at 1.53 points in PIPP-R, and we estimated a 10% loss, the sample size calculated is 29 participants in each group [5].

Given the scarce and heterogenous literature available on IVH [24], the populational behavior of this variable is unknown, with no references to calculate the sample size.

Therefore, the minimum estimated sample size to respond to the aims proposed is 35 subjects in each group.

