### 2.10. Outcomes

Primary outcome:
Premature infant axillary temperature.

Secondary outcomes:
Neonatal pain level.Intraventricular hemorrhage number of events.

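### The analysis tests an undefined temperature 'variation', while the outcome and sample size sections define and size axillary temperature, so the 0.16 SD, and on one reading the 0.2 °C margin, need not apply to what is tested

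*Protocol article*

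**What the plan says.** Section 2.2: "The study is designed as a non-inferiority randomized parallel clinical trial". The conclusion therefore rests on one margin for one variable.

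Section 2.10 gives the primary outcome as "Premature infant axillary temperature", with no mention of a change or a fluctuation.

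Section 2.5 states: "The primary outcome was the neonatal body temperature difference between KC prone position and KC lateral position". The trial is sized to "achieve an 80% statistical power with an α of 0.05" and "to detect a 0.3 °C difference in the body temperature", with an SD of 0.16, a margin of 0.2 and 10% loss, giving 35 per group. It does not say whether 0.16 is the SD of a level or of a change.

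Section 2.13 assesses effectiveness by "calculating axillary temperature variation" with Student's t-test or Mann–Whitney U. The same sentence analyses pain as a level. The word *variation* is not defined anywhere in the article.

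Table 1 schedules the infant's axillary temperature at t0 (10 minutes before kangaroo care), t1 (15 minutes in), t2 (30 minutes in), t2' (hourly in longer sessions) and t4 (30 minutes after the end). Section 2.8 monitors every session in the first five days.

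**The concern.** A temperature level, a change from t0 and a within-session fluctuation are different variables with different spreads. The sample size fixes one SD and one margin, and the analysis section appears to test a variable for which neither was stated. Because the same sentence treats pain as a level, *variation* can be read as a deliberate contrast.

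At stake are the meaning of the non-inferiority conclusion and the 80% power claim. A margin of 0.2 °C on mean temperature says how much colder the lateral group may be. It says nothing about how much more temperature may fluctuate. A later analysis plan could choose one reading, but that alone would not show that the SD and margin in section 2.5 were set for it.

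**Working it through.** **Inputs from section 2.5.** SD 0.16; difference 0.3 °C; margin 0.2 °C; power 80%; alpha 0.05 (sides not stated); loss 10%; 35 per group, hence 35 × 0.9 = 31.5 evaluable per arm.

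**1. The plan's own figure.** The distance between the stated difference and the margin is |0.3 − 0.2| = 0.1 °C. With one-sided 5%:

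n = 2 × (1.645 + 0.842)² × 0.16² / 0.1² ≈ 31.65 per arm; 31.65 / 0.9 ≈ 35.2.

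This reproduces 35 (rounding up at each step gives 36). The other bases tried do not: the same distance at one-sided 2.5% needs 41, or 46 with loss; margin 0.2 with a true difference of 0 needs 8, or 9 with loss, at one-sided 5%. So the plan's basis is SD 0.16, distance 0.1 °C, one-sided 5%. That the stated difference exceeds the margin is a separate matter.

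**2. What carries over under each reading of *variation*.**

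| Reading | Margin 0.2 °C | SD 0.16 |
|---|---|---|
| Loose wording for the between-group difference in temperature | applies | applies if 0.16 is the SD of a level |
| Change from t0 | applies: randomization makes the expected t0 equal in both arms, so the expected difference in change equals that in level | applies only if 0.16 is the SD of a change, or if r = 0.5 |
| Fluctuation within a session | does not apply | does not apply |

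**3. Size under the change-from-t0 reading.** Assumptions, since the article gives no correlation: 0.16 is the SD of a level, the SD is equal at both times, and r is the within-infant correlation.

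- SD of change = 0.16 × √(2(1 − r))
- SD of level adjusted for t0 = 0.16 × √(1 − r²)
- Power = Φ(0.1 / (SD × √(2/31.5)) − 1.645), where √(2/31.5) = 0.252

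| r (assumed) | SD of change | Power, change | SD adjusted for t0 | Power, adjusted |
|---|---|---|---|---|
| 0.3 | 0.189 | 67% | 0.153 | 83% |
| 0.5 | 0.160 | 80% | 0.139 | 89% |
| 0.7 | 0.124 | 94% | 0.114 | 97% |

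For r = 0.3, for example: 0.189 × 0.252 = 0.0477; 0.1 / 0.0477 − 1.645 = 0.45; Φ(0.45) = 67%.

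Over a wider range, r from 0 to 0.9 with 31 evaluable per arm, power for the change runs from 54% to over 99%. The required size with loss runs from 72 down to 8 per arm.

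**4. Why adjustment is safe.** 1 − r² = (1 − r)(1 + r). As 1 + r ≤ 2, this never exceeds 2(1 − r), and it never exceeds 1. With equal SDs, the t0-adjusted comparison is therefore never less precise than the change or the unadjusted level, apart from one degree of freedom.

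**5. Interval and alpha.** One-sided 5% corresponds to a 90% two-sided interval. With a 95% two-sided interval (one-sided 2.5%), SD 0.16, distance 0.1 °C and 31.5 per arm: 0.1 / (0.16 × 0.252) − 1.960 = 0.52, and Φ(0.52) ≈ 70%.

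**The case against.** *Variation* may be no more than loose wording for the difference between the groups. On that reading, with 0.16 the SD of a level, nothing is wrong beyond one word. This is possible and cannot be excluded, but the article does not establish it, and the primary analysis of a non-inferiority trial should not depend on a guess.

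Section 2.5 may also have taken 0.16 as the SD of a change, in which case the change-from-t0 reading costs no power. This stands: the article does not settle it, and the power range above is conditional on the other reading.

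The low end of the range also depends on the 0.1 °C distance. With a true difference of 0 and the full 0.2 °C margin, even r = 0.3 gives 0.2 / 0.0477 − 1.645 = 2.55, which is over 99% power. This stands as well. The range shows that the stated 80% is not tied to the tested variable, and no more.

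A reader might infer that the article names four rival outcomes, adding the aim's "modified kangaroo care lateral position on the thermal stability of preterm infants" and the between-position difference of section 2.5. It does not. Thermal stability is the construct in the aim, and the difference between positions is the contrast between arms. The conflict lies between temperature in 2.5 and 2.10 and *variation* in 2.13.

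A reader might also infer that an unblinded holder of the database could pick the measure after seeing results. Section 2.12 gives sole database access to the lead researcher and section 2.15 gives the main investigator unblinded access, but section 2.7 states that those who process and analyse the data are blinded. How these sections fit together is a question about blinding and is no part of this point.

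**Conclusion.** The mismatch is real and concerns the primary analysis. The variable tested in 2.13 is undefined and is not, as worded, the variable defined in 2.10 and sized in 2.5. Under the fluctuation reading, both SD and margin fail to apply. Under the change-from-t0 reading, the margin holds and only the SD is in doubt. Power is then 67% to 94% for assumed correlations of 0.3 to 0.7, given that 0.16 is the SD of a level with equal SDs at both times.

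It would be tempting to conclude that the trial is underpowered. The document does not support that: the error could run either way, and it vanishes at r = 0.5 or if 0.16 is already the SD of a change. The arithmetic behind 35 per group is not at fault on its own basis. The point should be corrected before analysis, with moderate confidence about its practical effect.

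**What to change.** Use one primary variable in sections 2.5, 2.10 and 2.13:

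- **Variable:** in-session axillary temperature in °C, one value per infant, stating which session is used or how sessions are combined.
- **Comparison:** lateral minus prone, by a linear model adjusted for the t0 value before the first session. Later t0 values follow earlier sessions in the allocated position and are not clean baselines.
- **Decision rule:** set the confidence limit for that difference against the 0.2 °C margin.
- **Alpha:** state it once and use it throughout. The figure of 35 per group matches one-sided 5%, that is, a 90% two-sided interval. If a 95% two-sided interval is preferred, restate the power (about 70% unadjusted, on the 0.1 °C distance and SD 0.16).
- **SD:** say which quantity 0.16 refers to. A value averaged over readings or sessions has its own SD, so 0.16 should be justified for the summary chosen or replaced.
- **Variation:** keep it only as a secondary description, with a definition.

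The cost is mainly wording. The t0 reading is already in Table 1, so no new data are needed. The sample size justification needs rewriting only if the interval or the SD changes.

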### 2.6. Randomization and Allocation

Participants will be recruited through non-probabilistic consecutive sampling.

Potentially eligible newborn patients will be identified in the research staff’s daily clinical practice or referred to them for eligibility assessment once they have been identified by clinicians who are not research staff.

Premature infants who meet all of the inclusion criteria and will be performing kangaroo care for the first time will be assigned to the experimental or control group on a simple 1:1 randomized basis, using a list of randomized numbers according to ID assignment from 1 to 70, using the random.org website.

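### Section 2.13 tests temperature and pain for a difference at p < 0.05 and never links the test to the non-inferiority margins on which the trial is designed and sized

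*Protocol article*

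**What the plan says.** - **Design (Protocol article, 2.2):** "The study is designed as a non-inferiority randomized parallel clinical trial".
- **Sample size (2.5):** the calculation uses "80% statistical power with an α of 0.05", a difference of 0.3 °C and an SD of 0.16, and "the non-inferiority margin was set at a 0.2 difference in body temperature". The section continues that "we estimated a 10% loss to follow-up, so the sample size calculated is 35 participants in each group". For pain it gives a difference of 0.83 points, an SD of 1, a margin of 1.53 PIPP-R points and 29 per group. It does not say whether alpha is one-sided or two-sided.
- **Analysis (2.13):** lateral and prone positions are compared by "calculating axillary temperature variation (Student’s t-test or Mann–Whitney U), level of pain", and the significance level is p < 0.05. The section mentions no margin, no shifted null hypothesis, no one-sided test and no confidence interval for the between-group difference. Its only 95% interval belongs to the descriptive analysis.
- **Analysis sets (2.13):** "Intention to treat (NNT) and protocol analyses will be performed". If the two disagree, deviations from the protocol are to be examined. The section does not say which set must meet the margin.

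**The concern.** The trial asks whether lateral kangaroo care is worse than prone by more than 0.2 °C. A t-test or Mann–Whitney U test, used in the ordinary way at p < 0.05, asks whether the two positions differ at all. The answers can disagree. A small deficit inside the margin can be statistically significant, and a non-significant result from imprecise data does not exclude a deficit beyond the margin. A Mann–Whitney p-value alone also gives no estimate in °C to set against 0.2.

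At stake is the primary conclusion, and the pain conclusion in the same way. A position that meets the trial's own standard of acceptability could be reported as a failure.

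**Working it through.** **Inputs.** From 2.5: margin 0.2 °C, SD 0.16 °C, difference 0.3 °C, alpha 0.05, power 80%, loss 10%, 35 per group. Evaluable per group: 35 × 0.9 = 31.5, taken as 31. Differences are lateral minus prone, so a negative value means that lateral is colder.

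**1. Reproduce the sample size.** n = 2 (z_alpha + z_power)² SD² / (distance to the margin)², with distance |0.2 − 0.3| = 0.1.
- One-sided 5%: 2 × (1.645 + 0.842)² × 0.16² / 0.1² = 31.65. Allowing for loss, 31.65 / 0.9 = 35.2, against 35 stated.
- One-sided 2.5%: 2 × (1.960 + 0.842)² × 0.16² / 0.1² = 40.2, so 41 evaluable and 45 to 46 with loss.
- Pain, one-sided 5%: 2 × (1.645 + 0.842)² × 1² / (1.53 − 0.83)² = 25.2, rounded up to 26; 26 / 0.9 = 28.9, so 29, as stated.

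Both stated sizes therefore come from a margin calculation at one-sided 5%. (The assumed 0.3 °C lies beyond the 0.2 °C margin; the formula works only because the distance is squared. That is a separate matter.)

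**2. Decision boundaries at 31 per arm.** SE = 0.16 × √(2/31) = 0.0406 °C.
- The 95% half-width is 2.000 × 0.0406 = 0.081 °C. The 90% half-width is 1.671 × 0.0406 = 0.068 °C.
- The written test is significant once the observed difference exceeds 0.081 °C in absolute size.
- Non-inferiority is shown if the observed difference is above −0.2 + 0.081 = −0.119 °C (95% interval) or −0.2 + 0.068 = −0.132 °C (90% interval).

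Observed differences from −0.081 down to −0.119 (or −0.132) °C are thus significantly lower and also non-inferior. For example, −0.10 °C gives p = 0.017 and a 95% interval from −0.181 to −0.019.

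**3. How often, at the planned SD of 0.16** (noncentral t, 60 degrees of freedom; simulation for the last column)

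| True difference (°C) | Written test significant | Non-inferior, one-sided 5% | Non-inferior, one-sided 2.5% | Both significantly lower and non-inferior (2.5% to 5%) |
|---|---|---|---|---|
| 0 | 5% | 99.9% | 99.8% | not tabulated |
| −0.05 | 23% | 98% | 95% | 18% to 20% |
| −0.10 | 68% | 78% | 68% | 36% to 46% |
| −0.20 | 99.8% | 5% | 2.5% | not tabulated |

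**4. The opposite error.** At a true difference of −0.2 °C the written test is non-significant in 100 − 99.8 = 0.2% of trials at SD 0.16. Larger SDs are assumptions that the article does not give: 27% at SD 0.3, 51% at 0.4 and 66% at 0.5. A margin test makes a false claim in 5% (or 2.5%) at any of these SDs.

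**The case against.** **The plan does not rule out a non-inferiority conclusion.** A reader might infer that the trial cannot conclude non-inferiority. The article does not support that. The margins are fixed in advance, and the data behind a t-test also give a mean difference and standard error, which is all that a comparison with the margin needs. Section 2.13 does not say that a significant p-value means lateral is worse, or that a non-significant one means non-inferior. This stands: the fault is a missing link between test and margin.

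**This is a condensed article, and a full analysis plan may hold the rule.** This stands only in part. The article is not silent: it names the primary test and its threshold, and these do not fit its own design.

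**False claims of non-inferiority.** A reader might infer that these are the main danger. At the article's own SD they are not (0.2%). They matter only if the SD is clearly larger than planned, which nothing in the article suggests.

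**The 68% depends on the deficit chosen.** This is fair: at 0.05 °C the figure is 23%.

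**Mann–Whitney need not be abandoned.** This is also fair. Its companion Hodges–Lehmann interval gives a shift in °C, which under a shift model is on the scale of the margin. Only the bare p-value is inadequate.

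**Disagreement between the analysis sets is addressed.** The article does say that deviations will then be examined. That is an investigation; it does not decide which result settles the claim.

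**Conclusion.** The point holds in this form: as written, section 2.13 applies a difference test at p < 0.05 to a question posed and sized as non-inferiority, and nothing in it connects the test to 0.2 °C or 1.53 points.

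At the plan's own SD the consequence is mainly a false failure. With a true deficit of 0.1 °C, the two rules give opposing messages in 36% (one-sided 2.5%) to 46% (one-sided 5%) of trials. These figures assume 31 evaluable infants per arm, one normally distributed temperature value per infant, SD 0.16, and that the section 2.13 test is read as a test of zero difference.

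It should be corrected before analysis because it concerns the primary decision rule and recurs for pain.

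**What to change.** In section 2.13:
- Estimate mean(lateral) − mean(prone) with a confidence interval. Claim non-inferiority for temperature only if the lower limit is above −0.2 °C, and for PIPP-R only if the upper limit is below +1.53 points. An unadjusted t-based interval is enough.
- Require this in both the intention-to-treat and per-protocol analyses already planned.
- If the data are non-normal, use an interval on the same scale (for example bootstrap or Hodges–Lehmann) in place of a bare Mann–Whitney p-value.
- State the one-sided alpha. A 90% interval (one-sided 5%) matches the calculation that reproduces 35 per group. If a 95% interval (one-sided 2.5%) is preferred, replace the 80% figure with the power it gives at 31 per arm: 99.8% at zero true difference and about 68% at a 0.1 °C deficit. Keeping 80% on the plan's own inputs would need about 41 evaluable per group, or 45 to 46 with loss.

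**Cost:** a change of wording and, under the 95% interval, a less favourable stated power. Requiring both sets to meet the margin can only lower the chance of a claim, so that should be acknowledged when power is restated.
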